### Data analysis

Descriptive statistics will be used to summarize the demographic and clinical characteristics in both intervention groups, and unpaired t-tests and chi-square tests will be used for comparisons. For all outcome measures, the Shapiro–Wilk and Levene tests will be used to measure the normality and homogeneity of the variance, respectively. If the assumptions of normality are met, a t-test will be employed, otherwise we will use Mann–Whitney U test to determine differences between the FtF and TR groups. Also, if the assumptions of normality are fulfilled, we will employ a repeated measures analysis of variance (RM-ANOVA), otherwise will be use Friedman’s test. Post-hoc pairwise comparisons will be used to determine the interventions effect over time for each group (FtF and TR). Cohen´s *d* will be used to report effect sizes for the CoP variables. To allow repeated measures analysis, missing data will be adjusted by 1) replacing with the non-missing average values for each variable/week, and 2) performing multiple imputations. Both methods will be used to make sure that the results were concordant. For all analyses, a *p*-value ≤0.05 will be considered statistically significant. All statistical analyses will be performed using IBM-SPSS 20.0 (SPSS Inc., Armonk, NY, USA).

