### Sample size

Using centre-of-pressure (CoP) sway area (CoP_area_) results from earlier studies [11, 22], to achieve an 80% statistical power with an alpha level of 0.05 and considering a standard deviation of 4.974 cm^2^ (after a 6-weeks intervention), we calculated a required minimum of 20 participants in each group (FtF and TR). This sample size includes a 5% attrition, which yields a total sample size of n = 40. Sample size calculation was performed using GRANMO (Institut Municipal d’investigació Médica, Barcelona, Spain). Once the investigative work has been carried out, the sample size will be verified again, and the estimation error will be adjusted. Feasibility of this study is ensured by our previous work with similar sample size, target population, outcomes, and funding [10].

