### Eligibility criteria

The inclusion criteria will be as follows: (1) levels I or II on the Gross Motor Function Classification System (GMFCS) [23] and on the Expanded and Revised Gross Motor Function Classification System (GMFCS-ER) [24]; (2) aged 7 to 14 years (both sexes) with CP type spastic hemiplegia; and (3) having mild or no cognitive impairment. Exclusion criteria will include patients with other than CP neurological disorders, epilepsy, and uncorrected vision or hearing. Participants with access to a Nintendo Wii at home before the intervention commences will be also excluded.

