### Allocation

Participants will be randomly assigned to either control (FtF) or experimental group (TR) with a 1:1 allocation as per a computer-generated randomization schedule stratified by site and the baseline score of the Action Arm Research Test (ARAT; < = 21 versus >21) using permuted blocks of random sizes. The block sizes will not be disclosed, to ensure concealment. This statistical methodology is adjusted to the randomized and block design, allowing feasibility and affordability to carry out this clinical trial.

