### Higher intensity rehabilitation: greater benefits?

High-intensity physiotherapy is necessary for optimizing motor learning and improve physical skills in patients with CP [33]. Regrettably, children and adolescents with CP typically receive limited physiotherapy sessions, which implies a lost opportunity to improve the functionality and quality of life of these patients during a critical period of their lives. It is important to note that the neural maturity of sensory systems responsible for the control of postural balance is sequential and dependent on age, reaching full maturity at 15–16 years [34, 35]. Therefore, providing as much rehabilitation time as possible during this age period is essential to generate motor function improvements that will profoundly impact their quality of life during adulthood. To our knowledge, the long-term benefits of high intensity physiotherapy delivered through telerehabilitation have not yet been stablished. The TR proposed in this protocol can offer a methodology to explore its potential benefits and determine the impact in patient’s daily life over the long-term.

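### Age, a plausible prognostic factor for sway area in children aged 7 to 14, is absent from the stated between-arm tests, and the planned baseline significance tests adjust for nothing

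*Protocol article*

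**What the plan says.** All references are to the protocol article.

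- **Eligibility criteria:** children "aged 7 to 14 years (both sexes) with CP type spastic hemiplegia".
- **Discussion, section on higher-intensity rehabilitation:** neural maturity of the sensory systems behind "the control of postural balance is sequential and dependent on age", with full maturity placed at 15–16 years. On that account every enrolled child is still maturing.
- **Allocation:** randomisation is 1:1, "stratified by site and the baseline score of the Action Arm Research Test". Age is not a stratum.
- **Data analysis, baseline:** characteristics are summarised by arm and "unpaired t-tests and chi-square tests will be used for comparisons". Nothing is said about acting on the results.
- **Data analysis, outcomes:** FtF and TR are compared by t-test, or by Mann–Whitney U if normality fails. Change over time is assessed by repeated-measures ANOVA or Friedman's test, with post-hoc comparisons over time for each group. No covariate is named.

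**The concern.** The primary outcome, CoP area, measures balance control. The protocol's own reasoning makes age relevant to balance control across the whole enrolled range. With about 20 children per arm and no stratification on age, the arms can differ in mean age by chance. Neither the t-test nor the Mann–Whitney U can take that into account.

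The only between-arm use that the plan makes of demographic data is significance testing. Under randomisation the null hypothesis of those tests is true by design, so a small p-value flags only a chance difference. A large p-value does not show that the arms are alike in a trial of this size. Neither result changes the outcome comparison.

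Two things are at stake. One is precision in a 40-child trial whose hypothesis is that TR works as well as FtF, where a wide interval limits what can be said about similarity. The other is interpretation if an age difference does turn up. Adding age at that point would look data-driven.

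**Working it through.** **The plan's own figure.** The Sample size section aims "to achieve an 80% statistical power with an alpha level of 0.05", "considering a standard deviation of 4.974 cm^2^ (after a 6-weeks intervention"), and states that "we calculated a required minimum of 20 participants in each group (FtF and TR"). It adds: "This sample size includes a 5% attrition, which yields a total sample size of n = 40".

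- Attrition step: 19/(1 − 0.05) = 20 per arm. This reproduces.
- The rest cannot be reproduced, because no target difference is given. Working backwards from 19 evaluable per arm, two-sided (an assumption, since sidedness is not stated): 4.974 × (1.960 + 0.842) × √(2/19) = 4.52 cm² by the normal approximation, or 4.65 cm² by the noncentral t. I use 4.65 as the difference detectable with 80% power.

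**Chance imbalance in age.** The age distribution is not given, so I assume an even spread, with SD = range/√12. The standard error of the difference in mean age is SD × √(2/20).

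| Assumed ages | SD (years) | SE (years) | P(difference > 1 year) | Difference needed for p < 0.05 |
|---|---|---|---|---|
| 7.0 to 14.0 | 2.02 | 0.64 | 12% | 1.3 years |
| 7.0 to just under 15 | 2.31 | 0.73 | 17% | 1.5 years |

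A 1-year imbalance would therefore pass a baseline t-test as non-significant. More generally, at 20 per arm that test has 34% power for an imbalance of 0.5 SD.

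**What a 1-year imbalance would do.** The shift in the unadjusted CoP-area difference is r × 4.974/SD(age), where r is the age–CoP correlation. The documents do not give r, so a range is assumed.

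- r = 0.3: 0.3 × 4.974/2.31 = 0.65 cm², or 0.74 cm² with SD 2.02.
- r = 0.5: 1.08 cm², or 1.23 cm² with SD 2.02.

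This is about 14–26% of 4.65 cm². Conditional on such an imbalance, with SD 2.02 and 19 per arm, the type I error is about 6.3% (r = 0.3) to 8.4% (r = 0.5). Averaged over all randomisations it stays at 5%.

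**Precision gained from age alone.** The SE ratio is √(1 − R²).

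- R² = 0.05: √0.95 = 0.975, a cut of 2.5%.
- R² = 0.25: √0.75 = 0.866, a cut of 13%.

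At 4.65 cm² and 19 per arm, with one degree of freedom deducted, power moves from 80% to 82% and 90% respectively.

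**Precision gained when baseline CoP area is already in the model.** Let b be the baseline-to-follow-up correlation of CoP area, and let age correlate equally (r) with both (assumptions). The partial correlation of age with the outcome is p = r(1 − b)/√[(1 − r²)(1 − b²)], and the further SE ratio is √(1 − p²).

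- b = 0.5, r = 0.5: p = 0.25/0.75 = 0.333, a further cut of 5.7%.
- b = 0.7, r = 0.3: p = 0.09/√(0.91 × 0.51) = 0.132, a further cut of 0.9%.

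In power terms, adding age moves 89.9% to 90.8–92.9% when b = 0.5, and 97.5% to 97.7–98.1% when b = 0.7 (r from 0.3 to 0.5).

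**The case against.** The strongest reply has four parts.

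**Validity.** A reader might infer that leaving age out makes the comparison biased or the test invalid. It does not. Under randomisation the unadjusted comparison is unbiased, keeps its type I error, and its standard error already allows for chance imbalance. This part stands. What remains is lost precision, and bias conditional on an imbalance that actually occurs.

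**Wording of the source.** A reader might also infer that the protocol names age as a predictor of CoP area, or uses the baseline tests to correct or certify balance. It does neither. The Discussion speaks of the maturity of sensory systems, not of CoP area, and gives no correlation. Data analysis gives the baseline tests no stated purpose beyond comparison. This part stands too. Age is a plausible prognostic factor, and the baseline tests are simply of no help.

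**Repeated-measures ANOVA.** With group as a factor, a group-by-time contrast would remove any constant age effect on sway. That is true of such a model, but the section states no group term. It describes post-hoc comparisons over time for each group and assigns the TR–FtF comparison to the t-test or Mann–Whitney U. This part does not dispose of the point.

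**Left to an analysis plan, and small.** Choice of covariates often belongs in a statistical analysis plan. Here, though, the article names tests that cannot take a covariate, so the unadjusted analysis is a stated choice. The gain is indeed small once baseline CoP area is modelled, and most of the benefit of adjustment would then come from the baseline value. That limits the size of the point but does not remove it.

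**Conclusion.** The point holds in a modest form. By the protocol's own account of maturation, age is a plausible prognostic factor for CoP area at 7 to 14 years. The stated between-arm tests ignore it, the randomisation does not stratify on it, and the baseline tests do nothing about it.

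The SE saving of 2.5–13% is what age would give as the only covariate, so the matching rise in power to 82–90% should not be taken as what age adds in general. Alongside baseline CoP area the further saving is about 1–6%. These ranges rest on assumed correlations, and the 12–17% chance of an imbalance above 1 year rests on an even spread of ages. None of those inputs is in the documents. The change is worth making because it costs almost nothing, not because the planned test is unsound.

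**What to change.** In Data analysis, replace the t-test or Mann–Whitney U comparison of CoP area with one pre-specified covariate-adjusted model (ANCOVA or a mixed model). Include age as a continuous covariate, ideally alongside baseline CoP area, and keep it whatever balance is observed. Say what replaces the rank-test fallback, since that test takes no covariate.

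Report baseline characteristics by arm descriptively, drop the t-tests and chi-square tests on them, and do not use baseline p-values to judge comparability.

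The cost is a sentence or two and one degree of freedom for age. Age is already needed for eligibility, so no new data are required. The change should be fixed before outcome data are seen.

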### Intervention timeline

Participants will be assessed at baseline, by the end of weeks 2, 4, and 6, and at weeks 8 and 10 (post-intervention follow-ups) using posturography and clinical measures.

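### A normality pre-test chooses the method, its longitudinal fallback (Friedman) has no arm term, and no baseline adjustment is named for the arm comparison

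*Protocol article*

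**What the plan says.** Data analysis applies Shapiro–Wilk and Levene tests to every outcome and lets the normality result choose the method, in two places.

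- **Between arms:** t-test if normal, otherwise Mann–Whitney U. No visit, change score, baseline covariate or stratification factor is named.
- **Over time:** "if the assumptions of normality are fulfilled, we will employ a repeated measures analysis of variance (RM-ANOVA), otherwise will be use Friedman’s test". No group factor or group-by-time term is named. The next sentence gives the purpose: "Post-hoc pairwise comparisons will be used to determine the interventions effect over time for each group (FtF and TR").

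Intervention timeline sets six assessments: "Participants will be assessed at baseline, by the end of weeks 2, 4, and 6, and at weeks 8 and 10". Baseline sway area is therefore planned for every child. The significance rule is "a *p*-value ≤0.05 will be considered statistically significant".

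The Introduction and Discussion pose two questions: whether the programme improves postural control, and whether TR is as effective as FtF.

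**The concern.** The tests and the switching rule are written into the article, so this is a stated choice and not a detail left to an analysis plan. Three things follow from it.

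1. Friedman's test ranks the visits within each child. RM-ANOVA can carry an arm factor and an arm-by-time term; Friedman's test can carry neither. Once the gate closes, no planned method compares the arms' time courses jointly. What remains over time is one result per arm, and two within-arm results do not make a between-arm test.
2. The gate rests on small samples, about 20 values if applied within an arm. Different visits of the same outcome may be analysed by tests that address different hypotheses, and Mann–Whitney as planned gives no difference with an interval.
3. In a trial of 40 children, an arm comparison without baseline gives up precision that needs no extra data.

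**Working it through.** **Inputs from the Sample size section.** "an alpha level of 0.05", sidedness not stated (two-sided taken here); "to achieve an 80% statistical power"; "considering a standard deviation of 4.974 cm^2^ (after a 6-weeks intervention"); 20 per arm including 5% attrition. The baseline–follow-up correlation r and the coefficient of variation (CV) of sway area are not given. Both are assumptions below.

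**The plan's own figure.** The attrition step is consistent: 19/(1 − 0.05) = 20. The 20 cannot be derived forward, because no difference is stated, only a pointer to earlier results ("Using centre-of-pressure (CoP) sway area (CoP_area_) results from earlier studies [11, 22"]). Solving backwards, δ = SD × (z₀.₉₇₅ + z₀.₈₀) × √(2/n) = 4.974 × (1.960 + 0.842) × √(2/19) = 4.52 cm², or 0.91 SD.

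**Friedman and the arms.** In one simulated trial, adding 50 cm² to every value in one arm left the statistic unchanged (9.04 both times). Over 2,000 simulated trials (19 per arm, six visits, correlation 0.6, normal data):

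- Common time effect of 4.5 cm², no arm difference: Friedman on the pooled children rejected in 100%.
- Same time effect plus an arm difference of 4.52 cm²: Friedman within arm rejected in 99% of trials in one arm and 100% in the other.

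So neither the pooled nor the per-arm results show whether the arms differ.

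**Type I error of the gate.** In the same simulations, including strongly skewed data, the t-test/Mann–Whitney switch rejected in 4.4–6.0% of trials with no arm difference, against 4.4–5.8% for the plain t-test.

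**How often the method switches.** Assumed: 20 per arm, six visits, correlation 0.7 between visits (log scale for lognormal data), Shapiro–Wilk per arm and visit, either arm's rejection switching that visit.

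| Data | At least one visit switches |
|---|---|
| Normal | 42% |
| Lognormal, CV 0.2 | 73% |
| Lognormal, CV 0.3 | 89% |
| Lognormal, CV 0.5–0.7 | 99% or more |

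The six visits would be split between the two tests in 84%, 72% and 41% of trials at CV 0.3, 0.5 and 0.7.

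**Value of baseline adjustment.** The residual variance becomes SD²(1 − r²), so the cut is r². Unadjusted 95% CI half-width, t on 36 degrees of freedom: 2.028 × 4.974 × √(2/19) = 3.27 cm². Adjusted: 3.27 × √(1 − r²). Power at δ = 4.52 cm² uses the normal approximation.

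| Assumed r | Variance cut | Half-width (cm²) | Power |
|---|---|---|---|
| 0 | 0% | 3.27 | 80% |
| 0.3 | 9% | 3.12 | 83.6% |
| 0.5 | 25% | 2.83 | 89.9% |
| 0.7 | 49% | 2.34 | 97.5% |

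**Dependence on scale.** With strongly skewed data, an additive effect and r = 0.6, ANCOVA on the raw scale had about 89% power against 97% for the planned route. With lognormal data and a log-scale effect of 0.91 SD, log-scale ANCOVA did better than the planned route: 80% against 76% (r = 0.3, CV 0.5), 87% against 75% (r = 0.5, CV 0.5) and 96% against 75% (r = 0.7, CV 0.7).

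**The case against.** The strongest defence is that Friedman is not the fallback for the arm comparison. Mann–Whitney is, and RM-ANOVA/Friedman serves the other aim, change over time within each arm. This stands. A reader might infer that non-normality leaves the trial with no valid between-arm comparison. The text does not support that: a valid randomised rank comparison remains wherever it is applied. What is lost is the joint longitudinal comparison, together with a planned effect size and interval for the arms.

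A reader might also infer that the plan ignores baseline. That is too strong. Baseline is one of the six assessments and would normally be a level of the RM-ANOVA or Friedman analysis, and the article does not say whether the arm tests use levels or changes. The fair statement is that no baseline adjustment is named for them. An article may leave covariates to an analysis plan, so this half of the point is weaker than the half about test choice.

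Nor do the calculations show an invalid gate, since error rates stay close to nominal. The switching rates depend on a CV that cannot be derived (an SD is given, a mean is not) and on testing per arm and visit, which the text does not specify. If changes from baseline were tested instead, Shapiro–Wilk would reject in about 23–37% of arms at CV 0.5–0.7, against roughly 50–69% for levels.

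**Conclusion.** The point holds in this form. The article fixes a normality-gated choice of method; its longitudinal fallback cannot compare the arms; the surviving arm comparison is a rank test without a planned estimate and interval; and no baseline adjustment is named for it. The consequences are unstable methods across visits and lost precision, not a false-positive problem.

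Adjustment would remove r² of the residual variance: 9%, 25% or 49% at r = 0.3, 0.5 or 0.7, and nothing at r = 0. The half-widths in cm² apply to a raw-scale analysis only. At least one switch would occur in about 42% of trials with normal data and in nearly all at CV 0.5 or above, under the per-arm, per-visit reading.

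It would also be wrong to infer that a better model by itself shows TR to be as effective as FtF. That claim needs a margin, and the article states none. The change should be made, but the trial is not invalid without it.

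**What to change.** Drop the normality-gated choice. Pre-specify one linear mixed model for CoP area at the post-baseline visits, with baseline value, arm, week, arm-by-week and the randomisation strata as far as 40 children allow. Fix the scale in advance, for example log with results reported as a ratio; using logs only if the data look skewed would bring back a data-driven switch. Take the TR–FtF contrast at week 6 with its 95% CI as the primary comparison. Keep a rank-based or permutation analysis as a sensitivity check.

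The cost is some wording and slightly more analysis work, with no extra children or visits. On a log scale the result is a ratio and not a difference in cm², and any margin used to support the claim that TR is as effective as FtF must be set on that same scale.

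### The effect over time is read from visit-pair tests run separately in each arm; such tests cannot show whether TR and FtF follow the same course, and unadjusted they also yield frequent false changes

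*Protocol article*

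**What the plan says.** All statements are in the protocol article, Materials and methods.

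- **Visits** (Intervention timeline): "Participants will be assessed at baseline, by the end of weeks 2, 4, and 6, and at weeks 8 and 10 (post-intervention follow-ups". That is six assessments.
- **Analysis over time** (Data analysis): if normality holds, "we will employ a repeated measures analysis of variance (RM-ANOVA), otherwise will be use Friedman’s test". The next sentence is "Post-hoc pairwise comparisons will be used to determine the interventions effect over time for each group (FtF and TR".
- **Threshold** (Data analysis): "For all analyses, a *p*-value ≤0.05 will be considered statistically significant".
- **Between-arm test** (Data analysis): "If the assumptions of normality are met, a t-test will be employed, otherwise we will use Mann–Whitney U test to determine differences" between FtF and TR. No visit is given, and the article does not say whether values or changes are compared.
- **Size** (Sample size): "we calculated a required minimum of 20 participants in each group (FtF and TR", including 5% attrition.

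The Introduction and Discussion give two hypotheses: the programme improves postural control, and the two delivery modes are equally effective. The article names no set of visit pairs, no adjustment, no rule that the pairs are tested only after a significant omnibus test, and no group-by-time term.

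**The concern.** Two separate problems follow from reading the time course arm by arm.

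The first is false change. Many visit pairs set against 0.05 can produce gains or losses between visits that are not there. An omnibus test placed first protects the pairs only when nothing changes at all. The trial expects improvement, and once there is a real gain the remaining pairs lose that protection.

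The second is discordance. A change that reaches 0.05 in one arm and misses it in the other says little about the difference between the arms. Yet a finding that a gain was kept under FtF and lost under TR would bear directly on the question of whether TR can replace FtF. Correcting the p-values within each arm does not remove this problem, because no quantity that compares the two courses is estimated.

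**Working it through.** **Inputs from the article.** Six visits; two arms; 20 per arm with 5% attrition, so 20 × 0.95 = 19 evaluable; threshold 0.05, taken as two-sided. The article states no error rate for the post-hoc tests, so there is no figure of its own to reproduce on this point. Its sample size cannot be reproduced either, because no detectable difference is given.

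**Assumptions.** Normal data; equal correlation between visits of 0.3, 0.5 or 0.7; identical true courses in both arms; one outcome in one condition. The article gives none of these.

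**Step 1: number of pairs.** C(6,2) = 15 per arm, 30 over both arms. Among weeks 2 to 10, C(5,2) = 10 per arm. At 0.05 the expected number of false pairs is 30 × 0.05 = 1.5 with no true change. The pairs are correlated, so the chance of at least one was simulated with paired t-tests at n = 19 per arm.

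**Step 2: combining arms.** With rate p in each independent arm, at least one arm is affected with probability 1 − (1 − p)², and exactly one arm with probability 2p(1 − p).

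**Step 3: no true change.**

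| Reading of the plan | Per arm | Per trial |
|---|---|---|
| All 15 pairs, unadjusted, ungated | 37-39% | 61-63% |
| Same, after a significant RM-ANOVA in that arm | about 5% | about 10% |
| Bonferroni over 15 (0.05/15 = 0.0033) | about 4% | about 8% |

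For example, at correlation 0.5 the ungated rate is p = 0.385, and 1 − 0.615² = 0.62.

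If only the five baseline contrasts per arm are tested, unadjusted, 28-34% of trials still have a false pair (n = 19 or 20; equal correlation 0.5 and 0.8, or serial correlation 0.7 and 0.9 per visit).

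**Step 4: real gain by week 2, then flat, gated.** Any significant change among weeks 2 to 10 is false.

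| Gain | Per arm | Per trial |
|---|---|---|
| 0.5 SD | 18-28% | 33-48% |
| 0.8 SD | 28-31% | 48-52% |

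At 0.8 SD and correlation 0.5, p = 0.291. Per trial this is 1 − 0.709² = 0.497, and in exactly one arm 2 × 0.291 × 0.709 = 0.413. With Bonferroni over 15 pairs the false-change rate is about 3% per arm, or about 5-6% of trials. Holm is slightly less strict and stays close to this.

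The result depends on the shape of the course. With a gain that builds evenly to week 6 and then holds (0.5 or 0.9 SD, n = 20), a false change among weeks 6, 8 and 10 occurs in 22-24% of trials ungated, 13-23% gated and about 2% after Bonferroni.

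**Step 5: discordance on a real gain.** Take the single pair baseline to week 6, with identical arms and a true 0.5 SD gain by week 2. It is significant in exactly one arm in 39-48% of trials gated and in 17-44% after Bonferroni. The formula shows why: if each arm had 80% power for that change, 2 × 0.8 × 0.2 = 32% of trials would show it in one arm only. At 50% power the figure is 50%. It becomes small only when power is very high or very low. With a 0.9 SD gain that builds to week 6 (n = 20), the gated rate is 0-25%.

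**Step 6: a direct comparison.** With identical arms and the gains that build to week 6, a group-by-time interaction test (Greenhouse-Geisser, n = 20 per arm) rejects in 4-5% of trials.

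**The case against.** The strongest reply is that much of this is inferred. The article does not say that all 15 pairs are tested, nor that the p-values are unadjusted; 15 is a maximum. A post-hoc test may imply a significant omnibus test first, and adjusted p-values can also be set against 0.05. The contrast list and the adjustment may sit in an analysis plan that is not shown. All of this stands. A reader might infer that the plan commits to 15 unadjusted tests per arm and would report false changes in most trials. The document does not support that reading.

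It is also fair that the within-arm tests serve the improvement hypothesis, that a separate between-arm test is planned, and that nothing says one-arm significance will be read as a difference between modes. The RM-ANOVA might include group as a factor, although the article does not say so and the Friedman fallback has no place for one. Much of the discordance in Step 5 is limited power to detect a real gain, not a false finding.

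None of this removes the core. The article does state that the effect over time is determined for each group separately, and the between-arm test it names is not tied to change over time or to a visit. Gating and adjustment, even if intended, leave discordance in place.

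**Conclusion.** The concern holds in a limited form. Separate within-arm pair tests cannot support a claim that TR and FtF have the same or different time courses, whichever adjustment is used. This follows from the stated method and does not depend on the simulations.

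The size of the false-change problem depends on details the article leaves open. It is large if all pairs are tested unadjusted (61-63% of trials with no change) and modest behind a gate when nothing changes (about 10%). Behind a gate it is large again when there is a real early gain and then a plateau (33-52%). It is small after Bonferroni or Holm. The correlations, gain sizes and shape of the course are assumptions. The point calls for a clearer analysis statement and does not undermine the trial's design.

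**What to change.** Replace the post-hoc sentence in Data analysis with the following.

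1. **Delivery-mode question.** From one group-by-time model, estimate the TR minus FtF difference in change with a 95% CI, for baseline to week 6 and for one named follow-up contrast. The article lists weeks 8 and 10 as follow-ups; the choice between them is the investigators', made before the data are seen. State how the same contrast is obtained if normality fails, since Friedman's test cannot provide it.
2. **Improvement hypothesis.** Keep the test of change from baseline to week 6, in each arm or pooled, and the same follow-up contrast, with Holm over this set. The strictest Holm threshold is 0.05/2 = 0.025 if pooled or 0.05/4 = 0.0125 if done in each arm, against 0.0033 for 15 pairs.
3. **All other visit pairs.** Report as descriptive estimates with CIs.
4. **Interpretation.** State that significance in one arm only is not evidence that the arms differ.

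The cost is wording only, with no new data or patients. Some visit-to-visit changes can no longer be called significant, and Holm costs a little power on the named contrasts. If an analysis plan already fixes the contrasts and adjustment, a sentence pointing to it, with items 1 and 4, would be enough.
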